## Abstract

**Background:**

Improving care at home for people with dementia is a core policy goal in the dementia strategies of many European countries. A challenge to effective home support is the occurrence of crises in the care of people with dementia which arise from changes in their health and social circumstances. Improving the management of these crises may prevent hospital admissions and facilitate better and longer care at home. This trial is part of a National Institute for Health Research funded programme, AQUEDUCT, which aims to improve the quality and effectiveness of teams working to manage crises in dementia.

**Methods/design:**

It is a pragmatic randomised controlled trial of an online Resource Kit to enhance practice in teams managing crises in dementia care. Thirty teams managing mental health crises in dementia in community settings will be randomised between the Resource Kit intervention and treatment as usual. The primary outcome measure is psychiatric admissions to hospital for people with dementia in the teams’ catchment area recorded 6 months after randomisation. Other outcomes include quality of life measures for people with dementia and their carers, practitioner impact measures, acute hospital admissions and costs. To enhance understanding of the Resource Kit intervention, qualitative work will explore staff, patient and carers’ experience.

**Discussion:**

The Resource Kit intervention reflects current policy to enable home-based care for people with dementia by addressing the management of crises which threaten the viability of care at home. It is based upon a model of best practice for managing crises in dementia designed to enhance the quality of care, developed in partnership with people with dementia, carers and practitioners. If the Resource Kit is shown to be clinically and cost-effective in this study, this will enhance the probability of its incorporation into mainstream practice.

**Trial registration:**

ISRCTN 42855694; Registered on 04/03/2021; Protocol number: 127686/2020v9; Research Ethics Committee, 09/03/2021, Ref 21/WM/0004; IRAS ID: 289982

**Supplementary Information:**

The online version contains supplementary material available at 10.1186/s13063-021-05995-y.

## Background

Worldwide around 47 million people live with dementia [1] including an estimated 850,000 people in the UK [2]. Services for people with dementia in the UK cost over £17 billion a year, even with savings of around £6 billion a year due to the contribution of family caregivers. In future decades, with an ageing population, increasing numbers of people with dementia are likely to live at home. As in many countries, improving dementia care is a key priority in England [3, 4], with home-oriented care a key objective of the National Dementia Strategy [5]. However, fluctuations in the health and social circumstances of the person with dementia and their family carers may lead to crisis, breakdown in home care and admissions to hospital or long-term care. Focused approaches to manage these problems may sustain care at home, improve quality of life and reduce costs.

Indeed, in one study, one in ten respondents reported a relative with dementia admitted to hospital unnecessarily due to lack of access to community support [2]. For the working age population with mental health problems, Crisis Resolution Teams, designed to avoid inappropriate hospital admission, have shown some reduction in hospital admissions and improvements in patient and caregiver satisfaction [6–10] although requiring better-defined service models [11]. In contrast, people with dementia and their carers experiencing crisis are often supported through a variety of different services varying in nomenclature, staff mix and operational procedure [12]. These services include Community Mental Health Teams, Crisis Resolution and Home Treatment Teams and generic older people’s rapid response teams. All these services are described in this paper as Teams Managing Crises in Dementia (TMCDs). Unlike services for younger adults, there appears to be less evidence and no guidance as to how such teams, or crisis resolution services for older people including those with dementia, should be designed or operate [13, 14].

People with dementia, caregivers, and practitioners appear to value a more coordinated approach to crisis management which is responsive to the unique features of each crisis [15]. Home Treatment Packages have been used to help teams manage crises for people with dementia and their family carers [16], with specialist older people’s crisis services identified as providing valuable expertise [17, 18]. A systematic review and a scoping exercise of crisis interventions in dementia found some evidence that specialist crisis teams effectively managed crises and reduced hospital admissions, although a more clearly defined model of best practice was needed [19]. This suggested that crisis intervention approaches could reduce admissions to psychiatric hospitals for people with dementia, but that stronger evidence to support their efficacy was required and this informed the development of the AQUEDUCT research programme.

AQUEDUCT is a National Institute for Health Research (NIHR) funded programme (RP-PG-0612-20004) designed to develop and evaluate a coherent model of crisis management in dementia care, reducing service variation and enhancing quality and effectiveness. Earlier parts of the programme involved a scoping review of the effectiveness of crisis interventions and a survey of crisis teams which confirmed some evidence of impact upon hospital admissions but with marked variations across services in England in the pathways to manage crises. It recommended a trial of a standardised care pathway and measurable intervention to provide better evidence [12]. Work with people with dementia, carers and practitioners in mental health services was undertaken using qualitative methods to develop a model of best practice and associated information and training materials for TMCDs [14, 20]. This model underpins a Resource Kit, developed in the AQUEDUCT programme, designed to provide guidance on best practice and achieve high-quality care.

The AQUEDUCT Trial aims to evaluate the Resource Kit in practice by conducting a randomised controlled trial with a representative sample of TMCDs across England, examining the impact upon hospital admissions, costs, and upon people with dementia, carers and staff compared with treatment as usual (TAU). A Consolidated Standards of Reporting Trials (CONSORT) flowchart of the trial is shown in Fig. 1.

**Fig. 1 Fig1:**
[figure not shown]
The AQUEDUCT Trial flowchart

## Method/design

The ‘Standard Protocol Items: Recommendation for Interventional Trials’ (SPIRIT) reporting guidelines have been used [21]—see the completed SPIRIT checklist (Additional file 1).

### Governance

Several groups have been established to oversee the trial. The Programme Management Group (PMG) oversees the full AQUEDUCT programme of research. It meets every 6 months and comprises the Chief Investigator (CI), all collaborators, researchers, and patient and public involvement (PPI) representatives. A Trial Steering Group (TSG) has met during set-up and thereafter at least annually. The TSG membership, approved by the funder, includes an independent Chair, at least two independent members with appropriate methodological and clinical expertise, one or two PPI representatives (a person with dementia or carer), the CI and other relevant members of the Trial Management Group (see below). Representatives from NIHR and from the trial sponsor (Nottinghamshire Healthcare NHS Foundation Trust) may also attend TSG meetings as active members. The role of the TSG is to: advise the CI on all aspects of the trial; provide overall supervision of the trial protocol, case report form, and statistical analysis; monitor trial progress; review relevant information from other sources related to the trial; review outputs and final reports; and if necessary, prematurely close the trial. The programme also has a standing PPI Reference Group that meets 6 monthly and is consulted regarding study development.

A Trial Management Group (TMG) has met monthly during the set-up of the trial and will then meet monthly or bimonthly, as appropriate and is accountable to the TSG for trial implementation and operation. It consists of key individuals directly involved in the development and delivery of the trial including the: CI; Trial Manager; collaborators; and experts by experience. The role of the TMG is to: monitor trial progress, ensure compliance with and adherence to the project plan; identify and resolve concerns regarding the intervention and research, including publication authorship; and consider and act on recommendations of the TSG and Research Ethics Committee.

A Data Monitoring Committee (DMC), independent of the sponsor and trial, will meet on at least two to three occasions and consists of a Chair, a statistician, and a clinical researcher. Membership of the DMC has been approved by the funding body. The role of the DMC is to: review the trial protocol and study materials regarding data management and analysis pertinent to their duties as the DMC; advise the TSG when it believes the trial protocol should be altered; and advise the TSG if the committee feels the trial should be prematurely closed [22].

The protocol for this present work package was developed in consultation with a Clinical Staff Reference Group, consisting of National Health Service (NHS) practitioners currently working in TMCDs across England, and the PPI Reference Group. All study documentation and participant recruitment procedures have been reviewed by the patient and public involvement representatives.

### Design

This is a pragmatic randomised controlled trial of an online Resource Kit for use by TMCDs. It is a two-arm, parallel-group, TAU controlled trial with treatment allocation of teams on a 1:1 ratio. The study aims to randomise 30 teams managing mental health crises in dementia in community settings between the Resource Kit intervention and treatment as usual. The null hypothesis is that there is no difference in the effect of crisis care management between teams using the Resource Kit and TAU. The primary outcome measure is admissions to psychiatric hospitals of people with dementia in the teams’ catchment area, assessed over a 6-month period after randomisation.

A feasibility study was conducted for the trial of this Resource Kit, including qualitative work to further shape the intervention by taking account of participant experiences and preferences [23]. This demonstrated that the Resource Kit was acceptable to and usable by practitioners working in TMCDs, who consistently reported that it accurately reflected their clinical practice. The feasibility study also identified certain difficulties experienced by people with dementia and their carers participating directly in research concerning their TMCD during a personal crisis. Building on these findings, iterative consultation with both the PPI Reference Group and the Clinical Staff Reference Group refined the trial of the Resource Kit in Crisis Management addressing both the content of the intervention itself and reducing the demands on participants and the scale of data collection processes. Implementation is designed to be mindful of pressures on the NHS and research feasibility due to the COVID-19 pandemic.

### Intervention

The Resource Kit intervention is an online and COVID-19 appropriate resource for TMCDs consisting of two components. The first is a Fidelity Measure which enables TMCDs to evaluate their practice according to 50 Best Practice Statements in relation to: the crisis service; rapid assessment and intervention; and service resources. The second is a Best Practice Toolkit, consisting of resources for teams to develop specific aspects of their practice. The Resource Kit is available as a password-protected online resource. The research team will provide initial training on completion of the Fidelity Measure and use of the Best Practice Toolkit. Each TMCD in the intervention arm will complete the Fidelity Measure before the intervention phase, to determine areas where practice could be improved. The TMCD will then implement at least four relevant templates from the Best Practice Toolkit, during the implementation phase of 6 months. The Fidelity Measure will be repeated at the end of the intervention phase (after 6 months). Further details about the intervention are provided in Fig. 2.

**Fig. 2 Fig2:**
[figure not shown]
The Resource Kit intervention

#### Treatment as usual

TMCDs in the control arm will not have access to the Resource Kit, will not complete the Fidelity Measure, and will not use elements of the Best Practice Toolkit during the 6-month implementation phase of the trial, but will continue to conduct TAU. Both intervention group and TAU group are otherwise free to undertake all usual interventions.

#### Adherence

Adherence to the overall study protocol by teams in both arms of the study will be supported through weekly contact with the research team throughout the study. Following training in the use of the Resource Kit, practitioners in the intervention arm will complete a self-administered assessment to inform the research team of their level of understanding of the intervention. Subsequent adherence to the intervention will be adjudged based upon the use of the Resource Kit by TMCDs in the intervention arm. Specifically, adherence constitutes: the application and reporting of a Fidelity Measure score at both baseline and follow up time points; uptake and ongoing utilisation of at least four templates from the Best Practice Toolkit; and participation in weekly contact with the research team for the study duration.

### Setting

The study will take place in NHS Trusts across England which provide mental health services to older people and aims to recruit 30 TMCDs. To be eligible, participating Trusts must provide mental health crisis services for older people and must confirm that they can report all psychiatric hospital admissions, for people with dementia, and provide precise details of local acute NHS Trust(s) which admit people with dementia from the TMCD’s geographical catchment area, as defined by postcode. All NHS Trusts must also confirm, in advance of trial commencement, that the Resource Kit can be used by TMCDs during the intervention, regardless of the trial arm (intervention or control) to which the team is subsequently allocated.

### Participants

#### Inclusion criteria

Participating teams must be managing dementia mental health crises, defined as providing urgent mental health assessment and intervention for people with dementia in the community. Participants will be staff members of the TMCDs and new referrals of people with dementia and their carers supported by these teams.

#### Exclusion criteria

To avoid contamination between intervention and control groups, teams will be excluded if they share: immediate management; administrative or core clinical staff; or the same office as another team in the study. Teams in services undergoing a major service reorganisation during the study period or in the near future will also be excluded. If a team leader who has been exposed to the intervention becomes lead for a team in the control arm of the trial, the latter team will be excluded.

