### Recruitment

#### Sites

NHS Trust sites will be recruited via professional and research networks across England, derived from earlier stages of the research programme. Participating Trusts will identify teams for inclusion in the study. Purposive recruitment will seek a diverse range of team service models and service user demographics, reflecting the earlier survey work undertaken in the study [12]. Each Trust shall confirm their capacity to undertake the trial by completing the Health Research Authority Statement of Activities, constituting a formal agreement with the study sponsor.

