#### Primary outcome measure

##### Psychiatric hospital admissions for people with dementia

All psychiatric hospital admissions for people with dementia from the TMCD catchment area (as defined by post codes) will be collated and reported at baseline and 6-month follow-up point for the preceding 6-month period.

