#### Random allocation

Following consent, each TMCD will be entered onto a web-based randomisation system and be randomly assigned to one of two arms, either using the Resource Kit or TAU with equal opportunity. The allocation will be determined by a computer-generated pseudo-random code using random permuted blocks of varying size, minimised by the number of people with dementia admitted to psychiatric hospital in the previous 6 months (either classified as low if the number is less than 25, or high if 25 or more) in each TMCD catchment area. The block size will not be disclosed to the research team. The randomisation system was set up and managed by the Research and Innovation team at the University of Nottingham (separate from the research team) in accordance with their standard operating procedure and is held on a secure server. The randomisation process is described in detail in a separate file and held securely within the statistics master file.

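### The contamination rule screens teams for shared managers, staff and offices but not for shared postcodes, although the primary outcome is counted by postcode catchment

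*Protocol article*

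**What the plan says.** Under *Exclusion criteria* the protocol article gives the rule's purpose, "To avoid contamination between intervention and control groups", and then its content: "teams will be excluded if they share: immediate management; administrative or core clinical staff; or the same office as another team in the study". Each of these tests concerns organisation. None concerns geography.

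The primary outcome is geographic: "All psychiatric hospital admissions for people with dementia from the TMCD catchment area (as defined by post codes) will be collated and reported". It is not limited to people whom the team saw. Acute/general hospital admissions are defined in the same way, and the *Statistical analysis* section uses the dementia population of each catchment as the offset.

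Three further statements bear on whether catchments could overlap:
- *Background* counts several kinds of service as a TMCD: "These services include Community Mental Health Teams, Crisis Resolution and Home Treatment Teams", together with generic rapid response teams for older people.
- *Sites* says that "Participating Trusts will identify teams for inclusion in the study", and that "Purposive recruitment will seek a diverse range of team service models".
- *Random allocation* makes the single team the unit: "each TMCD will be entered onto a web-based randomisation system and be randomly assigned to one of two arms".

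The article does not require catchments to be mutually exclusive, does not limit a Trust or an area to one team, and does not say to which team an admission from a shared postcode belongs.

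**The concern.** The rule protects against staff exposure crossing between arms. It does not protect the quantity on which the trial is powered. A community mental health team and a home treatment team can have separate managers, staff and offices, pass every listed criterion, and still serve some of the same postcodes.

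If such a pair is split between arms, each admission from the shared postcodes is one event entered in both arms. It adds nothing to the difference between arms, so the estimated rate ratio moves towards 1. The population behind the offset is shared in the same way, so the offset does not correct this. A Poisson or negative binomial model with one row per team also treats the two rows as independent when they contain the same events. Acute/general admissions are exposed in the same way.

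**Working it through.** **Inputs from the *Sample size* section:** 15 teams per arm; mean count per catchment 17 to 33 over 6 months; minimum important reduction 20%; target difference 7; two-sided 0.05; 90% power; Poisson counts. The extent of overlap is not given, so every overlap figure below is an assumption.

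**1. The plan's own figure.** Take 33 vs 26 with variance 33:

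n = 2 × 33 × (1.960 + 1.282)² / 7² = 14.2, so 15 per arm.

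Power at 15 = Φ(7/√(2 × 33/15) − 1.96) = Φ(3.337 − 1.96) = 91.6%.

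The stated 15 per arm reproduces from the upper end of the range.

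**2. Partial overlap.** Let k of 15 cross-arm pairs share a fraction f of their admissions. Shared admissions cancel, so the difference becomes 7 × (1 − f × k/15). Power = Φ(difference/2.098 − 1.96), where 2.098 = √4.4.

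| k of 15 pairs | f = 10% | f = 20% | f = 30% |
|---|---|---|---|
| 2 | 6.91, 91% | 6.81, 90% | 6.72, 89% |
| 5 | 6.77, 90% | 6.53, 88% | 6.30, 85% |
| 15 | 6.30, 85% | 5.60, 76% | 4.90, 65% |

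The last row is an extreme case in which every team overlaps with one in the other arm.

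**3. Full overlap in k cross-arm pairs.** Take a true 20% reduction from 33, and let the Kit's full effect reach the shared area:
- control mean = 33 × (1 − 0.2k/15); Kit mean = 26.4
- power = Φ(ln(control/Kit)/SE − 1.96), with SE² = 1/(15 × control) + 1/(15 × Kit)

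| k | Control mean | Rate ratio | ln ratio | SE | Power |
|---|---|---|---|---|---|
| 0 | 33.00 | 0.80 | 0.2231 | 0.0674 | 91% |
| 2 | 32.12 | 0.82 | 0.1961 | 0.0678 | 82% |
| 3 | 31.68 | 0.83 | 0.1823 | 0.0680 | 76% |

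This formula treats the two arms' counts as independent. Simulating the shared admissions as the same events in both arms gives 84% (k = 2) and 79% (k = 3), so the approximation is slightly pessimistic but the picture does not change.

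**4. How much overlap k implies.** Under 1:1 allocation of 30 teams, a given pair falls in opposite arms with probability 15/29 = 52%, ignoring blocks and minimisation. So k = 2 corresponds to about 2/0.517 = 3.9 fully coincident pairs among the 30 teams, and k = 3 to about 3/0.517 = 5.8: roughly 4 and 6 pairs, or 8 and 12 teams.

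**The case against.** The strongest reply is that overlap is conjecture. The article speaks throughout of the catchment of each team, and the minimisation, the offset and the sample size all treat one team as one area. The list of service types describes variation across England, and the search for diverse models describes the national sample; neither says that two services covering the same postcodes will be enrolled. The existing criteria probably remove some co-located teams. A fuller protocol exists and may say how catchments are drawn.

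Much of this stands. A reader might infer that double counting will happen, or that a large loss of power is to be expected. The document supports neither: it reports no overlap, and the larger losses need several fully coincident pairs split between arms. Nor is it right that the present criteria give the outcome no protection at all.

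What does not stand is that the point is mere condensation. The article writes out its contamination rule test by test, and the list has no test for the unit on which the outcome is counted. Giving each team an area does not make the areas exclusive.

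**Conclusion.** The point holds as a gap in the stated eligibility rule, not as a demonstrated bias. The text permits two teams with shared postcodes to enter opposite arms. If that happens, the rate ratio is diluted towards 1 and the rows are no longer independent.

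The size depends on an extent of overlap that the document does not give. Small overlaps in a few pairs cost a point or two of power (91–89% against about 92%). Two or three fully shared cross-arm pairs bring power to about 82% or 76%, from 91%, for a 20% reduction from 33. These figures assume Poisson variance and the upper end of the admission range. With no overlap there is no loss, and the sample size needs no change. This is a cheap improvement to the design.

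**What to change.** Add to the exclusion criteria that teams in the study must have non-overlapping postcode catchments for outcome counting, and compare the teams' postcode definitions at set-up, before randomisation. Then:
- Where two nominated teams overlap substantially, take one, or randomise them together as one unit with one admission count.
- Where only boundary postcodes are shared, assign each to one team before randomisation, for both the count and the offset. Excluding teams over a trivial boundary would be needlessly strict.
- If overlap comes to light after randomisation, keep both teams in the primary analysis and add a sensitivity analysis that omits the shared postcodes from both.

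The cost is one eligibility line and a small check at set-up. The *Setting* section does not say that Trusts already supply postcode lists, so these may have to be requested. A few nominated teams might need replacing from other sites.

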### Sample size

Information collected in different stages of the AQUEDUCT research programme, showed the average hospital admission count per TMCD catchment area over a 6-month period to be between 17 and 33. Following stakeholder consultation, a 20% reduction represented the minimum clinically significant difference in outcome. Therefore, 15 TMCDs will be required in each of the two study arms (30 in total) to detect a 7-point mean admission count difference between arms with 90% power at a two-tailed 0.05 significance level, assuming the count of hospital admissions follows a Poisson distribution. Stata 16 software was used for this power analysis. It is anticipated that no TMCD will withdraw from the study and that NHS Trusts will provide the required hospital admissions data for each TMCD; thus, the number of TMCDs required is unlikely to be influenced by lost information due to withdrawal. However, to manage risk of loss, additional team sites will be kept in reserve.

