### Statistical analysis

The data analysis will be conducted on an intention to treat basis. The treatment effects estimate (95% CI) on the primary outcome and the number of general hospital admissions will be quantified using Poisson regression with binary arm status as an exploratory variable and the size of the population with dementia within each TMCD catchment area as an offset. An over-dispersion check will be performed, and a negative binomial regression model will be used if there is evidence that the outcome variance is greater than the mean. The treatment effect estimates on TMCD practitioners’ and people with dementia and carers’ outcome measures will be explored using multilevel modelling with the TMCD as a level two analytical unit and baseline measures included as covariates [35, 36]. Skewed continuous outcome variables will be transformed for multilevel modelling, and nonlinear multilevel modelling will be performed for categorical outcomes. No interim analysis is planned, and safety and adverse event information will be presented descriptively. Missing values will be imputed via analytical modelling assuming missing at random status. Stata 17 will be used to analyse the data.

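### The leader-move rule excludes control teams after randomisation, in one arm only, and conflicts on a plain reading with the stated intention-to-treat analysis

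*Protocol article*

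**What the plan says.** Exclusion criteria opens with the purpose of its rules: "To avoid contamination between intervention and control groups, teams will be excluded if they share" management, staff or premises with another study team. Its last sentence then deals with a leader who has been exposed to the Resource Kit. If that person "becomes lead for a team in the control arm of the trial, the latter team will be excluded".

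Random allocation makes the team the unit of randomisation: after consent, "each TMCD will be entered onto a web-based randomisation system and be randomly assigned to one of two arms".

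Statistical analysis states the analysis principle without qualification: "The data analysis will be conducted on an intention to treat basis".

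Sample size assumes no loss of teams: "It is anticipated that no TMCD will withdraw from the study". It sets 15 teams per arm.

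Primary outcome measure defines the outcome as psychiatric admissions of people with dementia from the team's postcode catchment. Data collection has the relevant NHS Trust department, not the team, compile and report that count retrospectively.

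**The concern.** A criterion that refers to a team's arm cannot be applied at screening. It operates during follow-up, it is triggered by an event after baseline (a change of leader), and it can remove only control teams. Control teams that change leader need not resemble those that do not. Taking them out of one arm while leaving the other untouched means that the arms compared are no longer the arms that randomisation formed. The resulting bias could favour either arm.

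The second problem is that the analysis set is unclear. One section appears to remove a randomised team and another appears to keep it. If such a move happened, the choice between them would be made by people who know the team's allocation, since the rule cannot be applied without knowing it. The question should be settled in the text before any outcome data are seen.

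**Working it through.** **The passages side by side**

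1. *When the rule acts.* It applies to a team in the control arm. Under Random allocation, a team has an arm only after it is entered on the randomisation system. The exclusion is therefore post-randomisation.
2. *Which arm it acts on.* It names only the control arm. Nothing removes an intervention team because its leader leaves or is replaced. The exclusion is therefore one-sided.
3. *What intention to treat requires.* Each randomised team is analysed in its allocated arm whatever it received. An exposed leader arriving at a control team is contamination, which is a departure from allocated treatment and not a ground for removal.
4. *Whether the outcome would be missing.* It would not. The count is defined by postcode and reported by the Trust. Setting requires Trusts to confirm beforehand that they can report all such admissions. A change of leader does not affect this.
5. *Consistency with the sample size.* Sample size anticipates no withdrawals and expects Trust data for every team. A rule that discards a randomised team does not fit that expectation.

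**Size of the loss**

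Inputs from Sample size: 15 teams per arm, 90% power, two-sided 0.05, Poisson counts, average count between 17 and 33 per six months, a 20% reduction, and a 7-point difference.

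*Reproducing the plan's figure.* With λ1 = 33 and λ2 = 0.8 × 33 = 26.4 (a difference of 6.6, about 7):

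- n per arm = (λ1 + λ2)(1.960 + 1.282)² / (λ1 − λ2)² = 59.4 × 10.51 / 43.56 = 14.3, which rounds up to 15.
- The log-rate version, (1/λ1 + 1/λ2) × 10.51 / [ln(λ1/λ2)]², gives 14.4, also 15.

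The stated 15 per arm is reproduced from the top of the 17 to 33 range.

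*Share of the arm.* One excluded control team is 1/15 = 6.7%.

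*Power if control teams are dropped and not replaced.* The number dropped is an assumption, as the documents give none. Power = Φ( ln(33/26.4) / √[1/(33·n_c) + 1/(26.4·15)] − 1.960 ), where n_c is the number of control teams analysed:

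| Control teams analysed | Power |
|---|---|
| 15 | 91% |
| 14 | 90.3% |
| 13 | 89.3% |
| 12 | 88.1% |
| 10 | 84.9% |

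Losing one to three control teams costs at most about three percentage points. Precision is not the issue. What matters is who is compared and whether that is fixed in advance.

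**The case against.** The best defence is that 'excluded' may mean only that the team stops taking part. Exclusion criteria deals with eligibility and contamination, and Statistical analysis governs who is analysed. On that reading the Trust count of an excluded team would still be analysed as allocated, and nothing would conflict. This reading is possible, and the article nowhere says that the team's admissions are discarded. It also does not say that they are kept. The plain meaning of a criterion in that section is removal from the study. The wording therefore still needs reconciling, although it would be too strong to say that the analysis population cannot be applied.

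A second defence is rarity. An exposed leader would have to take over a participating control team within a six-month phase, and teams that share management or core staff are already kept out. This stands, and it lowers the priority.

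Two stronger readings are tempting but are not supported:

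- *Reserve teams.* A reader might infer that the reserve provision also breaches intention to treat. The text says only that "to manage risk of loss, additional team sites will be kept in reserve". It does not say that a reserve site displaces a randomised team or enters without being randomised. Reserve sites used before allocation, or newly randomised and analysed as allocated, are compatible with intention to treat. The mechanics may properly be left to the full protocol.
- *Reorganisation.* A reader might take "Teams in services undergoing a major service reorganisation during the study period or in the near future will also be excluded" as another in-trial exclusion because it mentions the study period. The reference to the near future makes sense only as a judgement made in advance, and the sentence names no arm. It reads naturally as a screening criterion for known or planned reorganisation.

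**Conclusion.** The point holds for the leader-move sentence alone. It is a post-randomisation exclusion confined to the control arm. On its plain reading it conflicts with the stated intention-to-treat analysis, and it is unnecessary for the primary outcome. Each team affected is 6.7% of the control arm. Power falls from about 91% to 88% if three control teams go, under the plan's Poisson assumption with means of 33 and 26.4.

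The bias has no determinable sign or size. A reader might try to estimate it by dropping a low-count team from the control mean, but the documents do not support that. The 17 to 33 range describes average counts from different programme stages, not the spread between teams. The planned model uses the catchment's dementia population as an offset, so a low raw count may only reflect a small catchment. Nothing in the article links leader moves to admission rates.

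The conclusion assumes that 'excluded' carries its ordinary meaning. If only participation was meant, the defect is one of wording and the same correction settles it. This should be fixed, but the narrow trigger keeps it below a must-fix.

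**What to change.** Reconcile Exclusion criteria with Statistical analysis by replacing the leader-move sentence with three statements:

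- every randomised team stays in the primary analysis in its allocated arm, with its Trust-reported admissions;
- a move of an exposed leader to a control team is recorded as a protocol deviation (contamination), with its date;
- affected teams are omitted only in a sensitivity analysis.

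The rules on shared management, staff and premises, and on reorganisation, can stay as screening criteria.

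The cost is a short wording amendment. The primary outcome needs no new data collection, because the Trust already supplies the count. The statistical price is slight dilution of the treatment effect from any contaminated control team, which the sensitivity analysis would help to show.
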